## Abstract

Vascular cognitive impairment no dementia (VCIND) is likely to develop into vascular dementia (VD) without intervention. The clinical efficacy of electroacupuncture (EA) for VCIND has been previously demonstrated. However, the neuroimaging mechanism of EA for VCIND has not been elucidated clearly. This trial is designed to provide solid evidence for the efficacy and neuroimaging mechanism of EA treatment for patients with VCIND. This ongoing study is an assessor-blind, parallel-group, randomized controlled trial. 140 eligible subjects will be recruited from the General Hospital of Ningxia Medical University and randomized into either the electroacupuncture (EA) group or the control group (CG). All subjects will receive basic treatment, and participants in the CG will receive health education performed weekly. Except for basic treatment and health education, participants in the EA group will receive treatment 5 times per week for a total of 40 sessions over 8 weeks. The primary outcome in this study is Montreal Cognitive Assessment (MoCA), and the secondary outcomes are Auditory Verbal Learning Test (AVLT), Stroop color-naming condition (STROOP), Rey–Osterrieth Complex Graphics Testing, and resting-state functional magnetic resonance imaging (rs-fMRI). All of the outcome measures will be assessed at baseline and 8 weeks of intervention. The medical abstraction of adverse events will be done at each visit. The results of this trial will demonstrate the efficacy and neuroimaging mechanism of EA treatment for VCIND, thus supporting EA treatment as an ideal choice for VCIND treatment. The trial was registered at the Chinese Clinical Trial Registry on 28 July 2018 (ChiCTR1800017398).

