## 2. Methods

### 2.1. Study Design and Setting

This study is an assessor-blind parallel-group RCT to explore the clinical efficacy and neuroimaging mechanism of EA for improving the cognitive function of VCIND patients. It will be performed in the General Hospital of Ningxia Medical University. A total of 140 eligible subjects will be randomly divided into 2 groups, namely, (1) EA group and (2) CG group, in a ratio of 1 : 1. All subjects will receive basic treatment with essential drugs, including hypotension, hypoglycemics, and antiplatelet and hypolipidemic drugs. In the CG group, they will only receive health education once a week, a total of 8 times. Except for basic treatment and health education, participants in the EA group will receive EA treatment that will be performed for 30 min per day and 5 days per week for 8 weeks. Operators with more than 5 years of clinical experience will perform the interventions. The 8-week intervention will be conducted. Outcome measurements include Montreal Cognitive Assessment (MoCA), Auditory Verbal Learning Test (AVLT), Test of Attentional Performance (TAP), Stroop color-naming condition (STROOP), Rey–Osterrieth Complex Graphics Testing (ROCFT), resting-state functional MRI (rs-fMRI), and adverse events. The planned flowchart for this trial is shown in Figure 1. The time point of assessment is provided in Table 1. Ethical approval has been provided with the Ethics Committee of the General Hospital of Ningxia Medical University in April 2018 (Additional file 1). Besides, General Hospital of Ningxia Medical University is also the project undertaking unit, which is responsible for coordinating the activities of all departments (e.g., trial registries, researcher training, informed consent of the participants, and data management). If there is an important protocol to be modified, it will notify the relevant parties to hold a coordination meeting. This protocol follows Standard Protocol Items: Recommendations for Interventional Trials (SPIRIT) (see Additional [Supplementary-material supplementary-material-1] in Supplementary Materials) [16].

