### 3.2. Interventions

All participants (2 groups) will be given health education once a week understanding the management of risk factors such as hypertension, diabetes, hyperlipidemia, and obesity and the drug management of these diseases. In addition, participants in the EA group will receive electroacupuncture treatment five sessions a week. Participants will be intervened in screen-separated personal space and will not be allowed to communicate with each other. Treatment will be conducted within 8 consecutive weeks.

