### 3.12. Investigation of Adverse Events and Safety

During the acupuncture treatment, subjects will be informed about adverse events such as local bleeding, subcutaneous hematoma, or pain associated and serious adverse events such as dizziness and palpitation in advance. Any adverse events and serious adverse events during treatment will be reported in the Case Report Form (CRF) and investigated, including its type and frequency, and appropriate treatments for the associated symptoms will be provided immediately to minimize serious adverse events. If a serious adverse event occurs, the case will be reported to the Data and Safety Monitoring Board (DSMB) of the clinical evaluation center of the General Hospital of Ningxia Medical University immediately and the blinding code will be broken. If necessary, even part or all of the trial will be suspended until further instructions are expected to be available. We will pay for the treatment of the subjects with serious adverse events until recovery.

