## Figures and Tables

**Figure 1 fig1:**
[figure not shown]
The planned flowchart of the trail. EA: electroacupuncture; HE: health education; MOCA: Montreal Cognitive Assessment; AVLT: Auditory Verbal Learning Test; TAP: Test of Attentional Performance; STROOP: Stroop color-naming condition; ROCFT: Rey–Osterrieth Complex Graphics Testing; rs-fMRI: resting-state functional MRI.

**Table 1 tab1:** The study schedule for enrollment, interventions, and assessments.

Items	Before enrollment −2 to −1 week	Intervention period 1–8 weeks	Outcome assessment 9 weeks
Inclusion criteria	×		
Exclusion criteria	×		
Informed consent	×		
Baseline	×		
Randomization and allocation	×		
Intervention		×	
Baker Depression Scale test	×		
MoCA	×		×
AVLT	×		×
TAP	×		×
STROOP	×		×
ROCFT	×		×
rs-fMRI	×		×
Adverse events		×	
Reasons of dropout and withdrawals		×	

**Table 2 tab2:** STRICTA checklist (details of intervention).

	Item	Detail
1. Acupuncture rationale	(1a) Style of acupuncture	Electroacupuncture based on traditional Chinese medicine theory
	(1b) Reasoning for treatment provided, based on historical context, literature sources, and/or consensus methods, with references where appropriate	Acupuncture points to be used in this study were Baihui (GV20) and Shenting (GV24) located at the head. Based on previous studies [21] and a large number of literature [22, 23], Baihui (GV20) and Shenting (GV24) will be mainly selected as acupuncture points for VCI treatment.
	(1c) Extent to which treatment was varied	Only EA group will receive electroacupuncture treatment

2. Details of needling	(2a) Number of needle insertions per subject per session	2
	(2b) Names of points used	Baihui (GV20) and Shenting (GV24)
	(2c) Depth of insertion, based on a specified unit of measurement	0.5 inches deep
	(2d) Response sought	“De qi” sensation
	(2e) Needle stimulation	Electroacupuncture
	(2f) Needle retention time	30 minutes
	(2g) Needle type	Sterilized stainless steel needle with the 0.3 ∗ 25 mm (Suzhou Medical Supplies Factory Co., Ltd., Jiangsu, China)

3. Treatment regimen	(3a) Number of treatment sessions	40 sessions (8 consecutive weeks)
	(3b) Frequency and duration of treatment sessions	30 minutes per day, 5 days per week

4. Other components of treatment	(4a) Details of other interventions administered to the acupuncture group	(a)All participants received routine treatment with essential drugs(b)All participants will be given health education once a week

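### Adverse events are recorded visit by visit, but the EA arm has at least 40 contacts and the control arm 8, so event frequencies by arm are open to unequal ascertainment

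*Protocol article*

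**What the plan says.** Adverse events are part of what the trial measures. Section 2.1 ends its list of outcome measurements with "resting-state functional MRI (rs-fMRI), and adverse events".

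Collection is described in three places:

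- The Abstract ties it to attendance: "The medical abstraction of adverse events will be done at each visit". The word *visit* is not defined.
- Section 3.12 opens on the acupuncture treatment and then says: "Any adverse events and serious adverse events during treatment will be reported in the Case Report Form". It asks for the type and frequency of events.
- Table 1 marks adverse events as a single block over weeks 1 to 8, the same for both arms, and leaves the week-9 assessment unmarked.

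Contact with the trial differs by arm. The Abstract says "participants in the EA group will receive treatment 5 times per week for a total of 40 sessions over 8 weeks", and Table 2 repeats the figure of 40. For controls, Section 2.1 says "In the CG group, they will only receive health education once a week, a total of 8 times". Section 3.2 adds a contact that both arms share: "All participants (2 groups) will be given health education once a week".

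Section 3.10 names MoCA and the cognitive secondary outcomes for the between-group comparison. It gives chi-square and Fisher tests for categorical variables without linking them to adverse events.

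**The concern.** If events are noted whenever a participant is seen, the arm seen more often has more occasions on which a passing symptom can be noted. Here that arm is always the EA arm.

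The problem lies with events that are not specific to needling. Section 3.12 names dizziness and palpitation, which could also occur in untreated participants aged 50 to 75 with vascular risk factors who take blood-pressure- and glucose-lowering drugs. To judge whether such events are related to EA, one needs the background rate in controls, and once-weekly contact may under-record that rate. Participants enter with a MoCA of 18 to 26, and memory is itself an outcome, so good recall over a week cannot be taken for granted.

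There is a possible knock-on effect. Section 3.12 gives dizziness and palpitation as examples of serious events, and has serious events reported to the DSMB and the code broken. More frequent recording in one arm could therefore mean more code breaks in that arm. The article gives no figures from which to size this.

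**Working it through.** **Contacts**

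- EA treatment sessions: 5 per week × 8 weeks = 40. This reproduces the figure in the Abstract and Table 2.
- Control contacts: 1 per week × 8 weeks = 8, as in Section 2.1.
- EA contacts including weekly health education (Section 3.2): 40 if given on treatment days, 40 + 8 = 48 if on separate days.
- Ratio: 40/8 = 5 to 48/8 = 6.

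**From contacts to recorded events**

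The ratio of contacts is not the ratio of recorded events, because a participant can report at one contact what happened before it. The article gives no event rate, duration or recall period, so the inputs below are assumptions:

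- true risk 20% in both arms, one event per affected participant;
- onset uniform over 56 days;
- the event can be reported for *w* days after onset;
- each contact in that window picks it up with probability *q*;
- EA contacts on days 1 to 5 of each week, control contact on day 5.

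Recorded risk = 0.20 × mean of [1 − (1 − q)^k], where *k* is the number of contacts in the window.

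*Worked case, w = 2.* For controls, 8 contacts × 2 days = 16 of the 56 onset days have one contact in the window and 40 have none. For EA, 32 onset days have two contacts, 15 have one and 9 have none.

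- q = 1.0: EA 0.20 × 47/56 = 0.168; control 0.20 × 16/56 = 0.057; ratio 47/16 = 2.9.
- q = 0.3: EA 0.20 × (32 × 0.51 + 15 × 0.3)/56 = 0.20 × 20.82/56 = 0.074; control 0.20 × (16 × 0.3)/56 = 0.017; ratio 20.82/4.8 = 4.3.

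Simulating the same model with 200,000 participants per arm gave 2.92 and 4.47 for these two cases. The gap between 4.5 and 4.3 is simulation error.

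**Expected participants with a recorded event, of 70 per arm** (EA v control, ratio in brackets). The true number is 0.20 × 70 = 14 in each arm.

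| w (days) | q = 0.3 | q = 0.6 | q = 0.9 | q = 1.0 |
|---|---|---|---|---|
| 2 | 5.2 v 1.2 (4.3) | 9.0 v 2.4 (3.7) | 11.3 v 3.6 (3.1) | 11.8 v 4.0 (2.9) |
| 7 | 11.0 v 4.1 (2.7) | 13.2 v 8.1 (1.6) | 13.5 v 12.2 (1.1) | 13.5 v 13.5 (1.0) |
| 14 | 12.6 v 6.5 (1.9) | 13.3 v 10.9 (1.2) | 13.5 v 13.2 (1.0) | 13.5 v 13.5 (1.0) |
| 56 | 12.8 v 9.7 (1.3) | 13.3 v 12.3 (1.1) | 13.5 v 13.3 (1.0) | 13.5 v 13.5 (1.0) |

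The assumed 20% cancels from the ratios. The best rows stop at 13.5 instead of 14 because the last contact in this layout is on day 54: onsets in the last 2 of 56 days are missed in both arms (0.20 × 54/56 × 70 = 13.5).

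**The case against.** The strongest reply is that no between-arm comparison of adverse events is planned. The aims are cognition and neuroimaging, Section 3.7 does not list adverse events as a secondary outcome, and recording type and frequency is descriptive. This stands as far as testing goes. A reader might infer that the chi-square or Fisher tests in Section 3.10 will be applied to adverse events and will be biased, but the article does not say so. What remains is that Section 2.1 calls adverse events an outcome measurement and Section 3.12 asks for their frequency. In a randomized trial those frequencies will be read by arm, tested or not.

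Second, *visit* is undefined. The article otherwise uses the word for the baseline evaluation in Section 3.5 and calls EA contacts sessions. It could mean a weekly visit common to both arms, and the Adverse Events Form mentioned in Section 3.9 is not shown. This is fair and rules out saying that the records *are* biased. However, Section 3.12 ties recording to the treatment period and opens on acupuncture, which points away from a common weekly enquiry.

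Third, a reader might take five times the contacts to mean nearly five times the recorded events. If a symptom were noted at 1% of contacts, for instance, 1 − 0.99^40 = 33% would have a record against 1 − 0.99^8 = 8%. That calculation allows no recall between contacts and so lies near the extreme. With a one-week reporting window the ratio is 1.0 to 2.7.

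Fourth, needle-site bleeding and hematoma can arise only with EA, so an excess of these is real and not an artefact. The distortion also runs against EA and would not flatter it. Both points stand.

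Finally, the unmarked week-9 cell in Table 1 applies to both arms alike and creates no imbalance. It matters only for completeness.

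**Conclusion.** The concern holds in a limited form. Followed as written, the article gives the EA arm 5 to 6 times as many scheduled occasions on which an event could be recorded, and describes no enquiry common to both arms. Frequencies by arm of events not specific to needling are therefore open to over-recording under EA.

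Under equal true risk the recorded ratio runs from about 1.0, where each weekly contact captures everything since the last, to about 4.5 by simulation (4.3 exactly) for two-day events picked up at 30% of contacts. These figures rest on assumed duration, pick-up and contact days. They show the possible range and do not estimate what this trial will see.

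The documents do not support a claim that a planned adverse event test is biased, that the distortion is certain, or that all excess events under EA would be artefacts. The primary MoCA analysis is not directly affected. This is an inexpensive improvement to the interpretation of safety data.

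**What to change.** 1. At the weekly health-education contact, which both arms already attend, ask every participant the same adverse event checklist covering the past week.
2. Ask it once more at the week-9 assessment, to cover the time since the last weekly contact.
3. Base any by-arm summary or comparison of adverse events on those records only.
4. List events noted at EA sessions, including needle-site events, separately and for the EA arm alone.
5. Reword Section 3.12 so that collection covers both arms, mark week 9 for adverse events in Table 1, and say which contacts *visit* refers to.

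The cost is a short form and slightly longer weekly contacts, with no added visits. Because Section 3.13 reports the trial as ongoing, the change should start in both arms on the same date by dated amendment. Records from before that date will not be on the common schedule and should be summarised apart. A common schedule equalises the occasions for reporting. It does not remove differences in reporting that come from participants knowing their group.

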## 1. Introduction

Vascular cognitive impairment (VCI) is cognitive dysfunction caused by cerebrovascular disease or factor, ranging from mild cognitive dysfunction (vascular cognitive impairment no dementia, VCIND) to overt dementia (vascular dementia, VD) [1]. Therefore, VCIND constitutes an intermediate stage between normal aging and vascular dementia [2]. VCIND manifests mainly cognitive deficits in at least one cognitive domain without impairment of activities of daily living (ADL) [3, 4]. A widely shared view is that up to 46% of patients with VCIND progress to VD after 5 years of diagnosis are without treatment [5]. Therefore, the early intervention of VCI, particularly VCIND, which would greatly reduce the chances of developing VD in later life, is particularly important.

In fact, previous research on EA has demonstrated that EA is an effective treatment to improve cognitive function by VCIND [6, 7]. One study revealed that, after 8 weeks of scalp EA treatment, the Mini-Mental State Examination score increased from 25.1 ± 0.9 to 28.4 ± 1.4, and the picture recognition increased from 10.1 ± 3.1 to 12.5 ± 3.1. Therefore, opposed to conventional treatment, EA is a promising and simple method of improving the cognitive function of the cognitive impairment patients [8]. In an animal model of cognition disorder, it has been supported that EA can improve memory and reduce neuroinflammation associated with dementia, which means to have neuroprotective effects for the brain [9]. However, the mechanism of EA in the treatment of VCIND remains unclear, especially in neuroimaging. Currently, rs-fMRI has been recognized as one of the most promising techniques for neuroscientists to decode brain activity, especially for elderly or patients with cognitive impairment [10, 11]. Neuroimaging studies have verified that the human brain has a default functional network (DMN) at rest [12]. Previous studies have demonstrated that cognitive disorders in subcortical vascular cognitive impairment (SVCI) are associated with alteration in resting DMN [13].

On the other hand, many studies have indicated that acupuncture regulates the activity of some cortical and subcortical brain regions, including the alteration of DMN [14, 15]. Therefore, we hypothesize that EA may improve the cognitive function of VCIND due to changes with DMN. Through this proposed randomized controlled trial (RCT), we plan to explore the potential mechanism of EA in improving cognitive function in patients with VCIND.

Therefore, during this trial, our main aim is to assess the effect of EA on cognition function for VCIND. Our second aim will be to explore the neuroimaging mechanism after EA treatment on VCIND.

## 2. Methods

### 2.1. Study Design and Setting

This study is an assessor-blind parallel-group RCT to explore the clinical efficacy and neuroimaging mechanism of EA for improving the cognitive function of VCIND patients. It will be performed in the General Hospital of Ningxia Medical University. A total of 140 eligible subjects will be randomly divided into 2 groups, namely, (1) EA group and (2) CG group, in a ratio of 1 : 1. All subjects will receive basic treatment with essential drugs, including hypotension, hypoglycemics, and antiplatelet and hypolipidemic drugs. In the CG group, they will only receive health education once a week, a total of 8 times. Except for basic treatment and health education, participants in the EA group will receive EA treatment that will be performed for 30 min per day and 5 days per week for 8 weeks. Operators with more than 5 years of clinical experience will perform the interventions. The 8-week intervention will be conducted. Outcome measurements include Montreal Cognitive Assessment (MoCA), Auditory Verbal Learning Test (AVLT), Test of Attentional Performance (TAP), Stroop color-naming condition (STROOP), Rey–Osterrieth Complex Graphics Testing (ROCFT), resting-state functional MRI (rs-fMRI), and adverse events. The planned flowchart for this trial is shown in Figure 1. The time point of assessment is provided in Table 1. Ethical approval has been provided with the Ethics Committee of the General Hospital of Ningxia Medical University in April 2018 (Additional file 1). Besides, General Hospital of Ningxia Medical University is also the project undertaking unit, which is responsible for coordinating the activities of all departments (e.g., trial registries, researcher training, informed consent of the participants, and data management). If there is an important protocol to be modified, it will notify the relevant parties to hold a coordination meeting. This protocol follows Standard Protocol Items: Recommendations for Interventional Trials (SPIRIT) (see Additional [Supplementary-material supplementary-material-1] in Supplementary Materials) [16].

### 2.2. Sample Size Calculation

In this procedure, the total score of the Montreal Cognitive Assessment Scale was invoked as the main effect index. The effect value was 0.9 in the treatment group and 0.725 in the control group [17], 0.8 in power and 0.05 in alpha. The sample size was estimated at PASS 24.0 software to be 116 cases, i.e., 58 cases in each group. Allowing 20% dropout rate, the total sample size was expected to be 140 patients (70 in each group).

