### 3.6. Primary Outcome

The primary outcome of this study is the changes in the score on MoCA from baseline to 8 weeks after intervention between the two groups and within groups. It is widely used for cognitive function assessment and can reflect the whole cognitive level of individuals. The MoCA has a maximum score of 30 points divided into eight parts, namely, visual space/executive ability (5 points), name (3 points), memory (5 points), attention (3 points), computing (3 points), language fluency (3 points), abstraction (2 points), and orientation (6 points). MoCA has excellent reliability and validity and is sensitive enough for clinical and research practice [25].

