### 3.10. Statistical Analysis

IBM SPSS Statistics 24.0 software will be used to conduct the whole data analysis by an independent statistician who is unaware of group assignments. All continuous variables will be presented as mean ± standard deviation (SD), and categorical variables will be presented as numbers (%). The statistical significance level is considered to be 95% CIs (two-sided alpha *P* < 0.05).

The effect of the intervention will be assessed as the change in outcome measures between the baseline and eight weeks (after treatment sessions end), using a repeated-measures analysis of variance (ANOVA) and chi-square test.

The difference in effect between the CG group and the EA group will be assessed by comparing changes in the MoCA score and secondary outcomes including language learning and memory function, attention function, executive function, and visuospatial function using the independent *t*-test or Mann–Whitney *U* test on continuous variables and chi-square test or Fisher's exact test on categorical variables.

Intention-to-treat analyses will be used for all outcomes. A multiple imputation method will be carried out to fill in missing data for outcomes.

The structure and function of functional magnetic resonance will be analyzed by SPM software based on the MATLAB platform. Neural network analysis techniques such as VBM, ROI, and ICA will be used to compare the differences in functional connectivity changes between groups by independent sample *t*-test. FDR correction will be used for multiple comparison and correction.

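### The sample size rests on two unitless values (0.9 and 0.725) that do not fit the continuous MoCA-change primary outcome and, read as proportions, do not give 80% power with 58 per group at the two-sided 5% level

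*Protocol article*

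**What the plan says.** Section 2.2 of the protocol article states that "the total score of the Montreal Cognitive Assessment Scale was invoked as the main effect index". Its inputs follow: "The effect value was 0.9 in the treatment group and 0.725 in the control group [17], 0.8 in power and 0.05 in alpha". The section reports 116 cases, 58 per group, and raises this to 140 (70 per group) for 20% dropout. It does not say whether the 5% level is one-sided or two-sided.

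Section 3.6 defines the endpoint: "The primary outcome of this study is the changes in the score on MoCA from baseline to 8 weeks after intervention". MoCA is scored to a maximum of 30 points. Section 3.10 sets the level for the whole analysis: "The statistical significance level is considered to be 95% CIs (two-sided alpha", at P < 0.05. It compares the change in MoCA between groups by independent t-test or Mann–Whitney U test. Tests for proportions are reserved for categorical variables, and the article defines no categorical efficacy outcome.

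**The concern.** A calculation for a mean change needs a difference in points and an SD, or a standardised difference. Section 2.2 gives one number per arm, both between 0 and 1, without a unit or SD. Those are the inputs of a two-proportion calculation. The article defines no responder threshold or effective rate to which such proportions could refer.

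There is a second difficulty. Even if the values are accepted as proportions, 58 per group looks too few for a two-sided 5% test with 80% power.

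At stake is the only statement of what the trial can detect. If the inputs belong to a different outcome, the 80% says nothing about the MoCA comparison that decides the trial. If they were also processed at a different significance level, the 80% does not hold for those inputs either.

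**Working it through.** **Inputs.** p1 = 0.9, p2 = 0.725, power 0.80, alpha 0.05 and 58 per group (70 with dropout) are from Section 2.2. The two-sided level is from Section 3.10. Allocation is 1:1 (Section 2.8). A 20% loss from 70 leaves 70 × 0.8 = 56. Normal quantiles are 1.960 (two-sided 5%), 1.645 (one-sided 5%) and 0.842 (80% power).

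**Step 1: can 58 be reproduced from two proportions?**

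Difference = 0.9 − 0.725 = 0.175, squared 0.030625. Mean proportion = 0.8125.

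Unpooled variance sum = 0.9 × 0.1 + 0.725 × 0.275 = 0.0900 + 0.1994 = 0.2894 (square root 0.5379). Pooled = 2 × 0.8125 × 0.1875 = 0.3047 (square root 0.5520). Arcsine effect h = 2·arcsin√0.9 − 2·arcsin√0.725 = 0.4605.

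Formulas for n per group:
- Unpooled z: (z_alpha + z_beta)² × 0.2894 / 0.030625
- Pooled z: (z_alpha × 0.5520 + z_beta × 0.5379)² / 0.030625
- Arcsine: 2 × [(z_alpha + z_beta) / h]²

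For example, unpooled two-sided is 7.849 × 0.2894 / 0.030625 = 74.2, and unpooled one-sided is 6.183 × 0.2894 / 0.030625 = 58.4.

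| Method | Two-sided 5% | One-sided 5% |
|---|---|---|
| Pooled z | 76.9 | 60.5 |
| Unpooled z | 74.2 | 58.4 |
| Arcsine | 74.0 | 58.3 |

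With continuity correction the two-sided figure is 88. No two-sided variant gives 58. Unpooled z and arcsine at one-sided 5% come close, although 58.3 or 58.4 would normally be rounded up to 59.

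**Step 2: two-sided power for 0.9 versus 0.725.**

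Unpooled: Φ(0.175 × √n / 0.5379 − 1.960). Pooled: Φ[(0.175 × √n − 1.960 × 0.5520) / 0.5379].

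| n per group | Pooled z | Unpooled z |
|---|---|---|
| 56 | 66.4% | 68.2% |
| 58 | 68.0% | 69.8% |
| 70 | 76.1% | 77.7% |

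Arcsine agrees with unpooled z to within 0.1 point. At 58 per group, exact enumeration gives 70.2% for the z test and 60.3% for Fisher's test.

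**Step 3: other readings of 0.9 and 0.725.**

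- *Standardised effects, difference 0.175:* n = 2 × 7.849 / 0.030625 = 513 per group (514 by the t-test). Power at 58 is about 15%.
- *Means in MoCA points, difference 0.175:* with 58 per group the detectable standardised difference at 80% power, two-sided, is 0.52. The SD would have to be 0.175 / 0.525 = 0.33 points on a 30-point scale.

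Neither is a plausible basis for 58.

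**Step 4: what the design can detect on its primary outcome.**

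Normal approximation: d = (1.960 + 0.842) × √(2/n), which gives 0.529 for 56, 0.520 for 58 and 0.474 for 70. The t-test values are 0.534, 0.525 and 0.477. Turning these into points needs an SD of change, which the article does not give. As an assumption only, an SD of 2 to 3.5 points gives 0.534 × 2 = 1.1 to 0.534 × 3.5 = 1.9 points with 56 per group, and 0.477 × 2 = 1.0 to 0.477 × 3.5 = 1.7 points with 70.

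**The case against.** The article never calls the values rates, and the cited source is not available here. A condensed article may also omit an SD or a definition that the full protocol contains. This stands in part: reading the values as proportions is a strong inference, not stated text. The conclusion does not depend on it alone, because the other readings in Step 3 fail by a wider margin. Nor does it rest on an omitted SD. The printed inputs, level and sample size do not fit together.

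Section 2.2 does not state sidedness, so a reader might infer that a one-sided test was demonstrably used. The documents do not show that. The match is approximate, depends on the formula (pooled z gives 60.5), and is only the likeliest explanation.

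A reader might also infer that the trial is underpowered for its primary outcome. That does not follow. The 68 to 70% concerns a binary comparison that the article does not define. For MoCA change, the same numbers give 80% power for a standardised difference of roughly one half. Nor would a null result be uninterpretable, because the confidence interval for the difference in MoCA change would show what has been excluded.

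Finally, 56 per group is not the planned analysis set. Section 3.10 specifies intention-to-treat with multiple imputation, so all 140 are analysed. Imputation does not fully restore lost information, so the effective precision lies between the figures for 56 and 70. Even at 70, power for 0.9 versus 0.725 stays below 80%.

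**Conclusion.** The point holds as a failure of justification. Section 2.2 does not size the outcome defined in Section 3.6 and tested in Section 3.10, and its stated 80% power is unsupported for that outcome.

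If the values are proportions, 80% power at two-sided 5% needs about 74 to 77 per group rather than 58. Power is about 68 to 70% at 58 and about 76 to 78% with all 70. These ranges cover pooled z, unpooled z, arcsine and, at 58 per group, the exact z test. Continuity correction or Fisher's test would be less favourable. The result rests on two assumptions: that the values are proportions, and that the two-sided level of Section 3.10 governs the power claim. The second is what the article says for its analysis.

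What remains unknown is whether 140 patients suffice for a worthwhile difference in MoCA change. The article gives neither that difference nor the SD needed to judge it.

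**What to change.** Keep 140 and rewrite the paragraph in Section 2.2. Delete the claim of 80% power for 0.9 versus 0.725 and replace it with a statement on the primary outcome, for example:

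*With 70 patients randomised per group, a two-sided 5% comparison of MoCA change has 80% power for a standardised difference of about 0.53 if 20% are lost (56 per group) and about 0.48 if all 70 contribute full information. The intention-to-treat analysis with multiple imputation lies between these. With an SD of change of [value, source], this corresponds to [range] points.*

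The SD must come from a cited source, and the text should say why a difference of that size is plausible and worth detecting. If a response rate is kept as an additional outcome, define the responder and state its two-sided power.

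The cost is one reworded paragraph and a search for an SD of change. No extra patients are needed. The drawback is that the stated power becomes less favourable than the present 80%. Section 3.13 describes recruitment as ongoing, so on the article's account the correction can be made before results are known.
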